### Study follow-up

The time zero is the first dispensation date of methadone, buprenorphine/naloxone, or SROM. For initiator analysis, follow-up ends at the earliest of outcome, death, loss to follow-up, 24 months after time zero, or December 31, 2022. For per-protocol analysis, we will censor at additional events: (i) treatment switch or falls OAT dose below the key benchmark, and (ii) individuals initiate taper or violate eligibility criteria, such as being pregnant, or incarcerated, or had received cancer or palliative care (see Table 3).

However, for sub-populations (ix) and (x), where treatment is considered a time-varying exposure and individuals may be consistent with both treatment strategies up to 30 days of OAT episode, we will apply the ‘clone-censor-weight’ approach to emulate the per-protocol target trial.[59,60] In this approach, each individual will be replicated into two clones, one for each treatment strategy. When individuals are no longer consistent with the assigned strategy due to a treatment switch, taper initiation, or violation of eligibility, we will artificially censor the corresponding clone at that time. For the clone assigned to the switch to SROM group, individuals will remain uncensored if they switch to SROM within 30 days of OAT episode, and be censored at day 30 if they have not switched by then (see Table 3).

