### Key measures

For sub-populations (i) to (viii), the primary exposure is the initiation of OAT with the dispensation of SROM, methadone and buprenorphine/naloxone in an initiator analysis framework. To compare the treatments at key dosing benchmarks, we will follow individuals receiving at least one dispensation of the following dosages per week. The key dosing benchmarks are aligned with BC clinical guidelines and previous literature:[6,58]

**Week 1:** SROM (≤240 mg), methadone (≤40 mg), and buprenorphine/naloxone (≤16 mg/4 mg).

**Weeks 2–3:** SROM (≥140 mg), methadone (≥30 mg), and buprenorphine/naloxone (≥12 mg/3 mg).

**Week 4 and beyond:** SROM (≥480 mg), methadone (≥80 mg), and buprenorphine/naloxone (≥16 mg/4 mg).

For sub-populations (ix) and (x), two treatment groups in per-protocol analysis framework will be defined as follows: individuals who switch to SROM within 30 days of initiating OAT with buprenorphine/naloxone or methadone, respectively, versus those who remain on their initial OAT type. Due to the lack of inpatient information on OAT dosing in our linked database, we will assume OAT receipt prior to hospitalization is continued daily throughout the duration of hospitalization.[6] Time to OAT discontinuation and all-cause mortality will be primary outcomes of interest for the initiator analysis. OAT discontinuation is defined as no OAT dispensation for ≥5 days for methadone and SROM, and ≥6 days for buprenorphine/naloxone. Additionally, time to overdose-related acute care visits (identified using ICD-10 codes T40, T42.4, and T43.6) will be assessed as a secondary outcome. The per-protocol analysis will assess the same set of outcomes: time to all-cause mortality, overdose-related acute care visits and OAT discontinuation.

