### Per-protocol analysis

We will conduct a per-protocol analysis to estimate treatment effects under sustained adherence at key dosing benchmarks, complementing the initiator effect.[86] To control the selection bias due to artificial censoring, we will consider two censoring models along with the propensity score models: (i) accounting for treatment switching, receipt of dose below key benchmark, and (ii) accounting for death, loss to follow-up, protocol violation by initiating pregnancy, dose taper, incarceration, or receipt of cancer or palliative care (see Table 3 for outcome specific censoring mechanism). Dose tapering is defined as two consecutive daily dose reductions without an intervening increase. Both censoring weights will be estimated using the approach described in the Initiator analysis section earlier. Final weights will be the product of the stabilized inverse probability of treatment weights at time zero and the post-baseline inverse probability of censoring weights, truncated at the 99th percentile. In the marginal structural model, we will apply a pooled logistic regression approach incorporating the final weights. The fitted model will be used to compute hazard ratios, risk differences, and risk curves. Compatibility intervals and curves will be computed using the approach described earlier. For sub-populations (ix) and (x), the censor-weighting approach will be similar, but we will apply a modified censoring mechanism as described in Table 3.

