## Figures and Tables

**Fig 1. F1:**
[figure not shown]
Construction of treatment episode for opioid agonist treatment for comparing slow-release oral morphine versus methadone and buprenorphine/naloxone

**Table 1: T1:** Key components of the emulated target trials on comparing the initiation of SROM versus methadone and buprenorphine/naloxone to treat people with opioid use disorder using the observational data

Protocol components	Hypothetical target trial	Emulation of the trial from BC health administrative data
Eligibility criteria	Adults aged 18 years or older who initiated OAT with MET, BNX, or SROM between June 1, 2017, and December 31, 2022. Individuals must not be pregnant or incarcerated and have no history of cancer or palliative care.	The same. To identify people who achieve better outcomes from SROM compared to MET and BNX, we will construct ten study populations to emulate the target trials (see Table 2 for details).
Treatment strategies	*For the study population (i) to (viii)* ITT: Initiating OAT with (1) MET, (2) BNX, and (3) SROM. PP: Receipt of at least 1 dispensation of optimal doses*: week 1: MET (≤40mg), BNX (≤16mg/4mg), SROM (≤240mg); weeks 2 through 3: MET (≥30 mg), BNX (≥12mg/3mg), SROM ((≥140mg); week 4 and beyond: MET (≥80mg), BNX (≥16 mg/4 mg), SROM (≥480 mg)[6] *For the study population (ix)* (1) Switching to SROM within 30 days of BNX initiation, (2) Staying on BNX. *For the study population (x)* (1) Switching to SROM within 30 days of MET initiation, (2) Staying on MET.	*For the study population (i) to (viii)* Treatment initiator effect and PP effect of the same strategies as proposed in the target trials. *For the study population (ix) and (x)* Same strategies as defined in the target trials.
Assignment procedures	Randomization. Prescribers, healthcare teams, and individuals are aware of the treatment status.	Individuals will be classified into treatment strategies based on dispensation records. Prescribers, healthcare teams, and individuals are aware of the treatment status.
Time zero	Date of randomization	Date of first OAT dispensation
Outcomes	Time to OAT discontinuation, along with the time to all-cause mortality and overdose-related acute care visit as the secondary outcomes.	Same.

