Treatment switch		C_3_		C_3_		C_3_
The overdose-related first acute-care visit					outcome	outcome

a. end of study follow-up is either Dec 2022 or 24 months from time zero, whichever occurs earlier C_1_, C_2_, and C_3_ indicate different censoring mechanism: C_1_: censoring due to end of study follow-up; C_2_: censoring due to death (not the all-cause mortality outcome), loss to follow-up, deviation from the trial exclusion criteria such as initiation of pregnancy, incarceration, dose taper, cancer or palliative care, leaving out of BC. Dose taper will be defined as two consecutive daily dose decreases (without intervening increase); C_3_: censoring due to deviation from the dosing protocol as mentioned in the key measures section, including treatment switching. Censoring for violating dosing protocols will not be applied to the study sub-populations (ix) and (x), as defined in Table 2. For the clone designated for switching to SROM in these sub-populations, individuals will be censored at day 30 if they remain on the initial OAT beyond 30 days, but will not be censored if they switch to SROM within 30 days of initiation; Separate censoring models will be used for C_2_ and C_3_.

**Table 4. T4:** Time fixed and time-varying covariates to estimate the inverse probability of treatment and censoring weights

Variable	Category	How the variable is defined and measured
*Socio-demographic factors*		
Age	Continuous	Based on birth date information from the client registry.
Sex	Male/Female	Based on medical records that record sex.
Living in rural region	Yes/No	Based on the population of the assigned local health area[65]
Homelessness/unstable housing in past 5 years^‡^	Past year, Past 1–5 years, Never/>5 years	Defined through International Classification of Diseases (ICD) 10: Z59.0, Z59.1 from physician billing or hospital discharge records or 3 consecutive records of no fixed address from Social Development and Poverty Reduction (SDPR)
Incarcerated in past year^‡^	Yes/No	Admission to BC correctional facilities and identified through records in the past year from the provincial corrections database.
Receipt of income assistance in the past year^‡^	Yes/No	Identified through records in SDPR and PharmaCare plan information on medication dispensations, using records within the past year.
Calendar year of time zero	2010 to 2022	Determined based on the dispensation date from PharmaNet.
*Comorbidity*		

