**Variable definition**		
Alternative optimal doses using 1:8 and 1:4 from MET to SROM conversion rate.[5,9]	1. Week 1: SROM (≤320 mg), MET (≤40 mg), and BNX (≤16 mg/4 mg); Weeks 2–3: SROM (≥240 mg), MET (≥30 mg), and BNX (≥12 mg/3 mg); Week 4 and beyond: SROM (≥640 mg), MET (≥80 mg), and BNX (≥16 mg/4 mg). 2. Week 1: SROM (≤160 mg), MET (≤40 mg), and BNX (≤16 mg/4 mg); Weeks 2–3: SROM (≥120 mg), MET (≥30 mg), and BNX (≥12 mg/3 mg); Week 4 and beyond: SROM (≥320 mg), MET (≥80 mg), and BNX (≥16 mg/4 mg).	PP
OAT discontinuation: 14 days	Alternative discontinuation thresholds have been defined in other studies.[88]	Both
OAT discontinuation: 30 days		Both
Outcome: all-cause acute care visits	In 2023, opioid-related poisonings resulted in 17 hospitalizations and 78 ED visits per day in Canada, marking a 16% increase compared to 2022.[89] Repeat ED visits (two or more) for OUDs within a year rose from 26% to 34% between 2018 and 2022 in Alberta, Ontario, and the Yukon.[90] Time to all-cause acute care visits will be considered as another outcome. We will repeat the statistical analysis for this outcome to evaluate the impact of alternative outcome on our results. Other components of the target trial and emulation process will remain the same.	Both
No truncation at 24 months of follow-up	While this redefining follow-up may cause instability in the weights of statistical analysis, the non-truncation at 24 months is to confirm the results.	Both
Alternative definition of prevalent new users: (i) no OAT dispensation in past 14 days, and (iii) no OAT dispensation in past 30 days, and (iii) no OAT dispensation in past 90 days.	To account impact of alternative definition of prevalent new users on our results. Three study population will be defined accordingly to assess the impact of eligibility criteria.	Both
No episode discontinuation at dose tapering ^f^	To include periods of time in which individuals wished to reach a state of abstinence.	PP
No episode discontinuation at receiving cancer or palliative care	To include individuals discontinuing treatment after receiving cancer or palliative care	PP
Composite outcome: Overdose-related acute care visits or OAT discontinuation	Instead of considering separate outcomes of overdose-related acute care visits and OAT discontinuation, we will consider the composite outcome of any of the two events. The other components of emulation will remain the same.	Both
Model specification		

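### Per-protocol mortality is censored at receipt of cancer or palliative care, so it estimates mortality without such care, not all-cause mortality; sub-populations (ix) and (x) have no other main analysis

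*Protocol article*

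**What the plan says.** Absence of a cancer or palliative care history is an entry criterion (Study population; Table 1). The plan also makes receipt of such care after time zero a per-protocol censoring event, in three places:

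- Study follow-up censors people who "violate eligibility criteria, such as being pregnant, or incarcerated, or had received cancer or palliative care".
- Per-protocol analysis puts it in the second censoring model, together with death, loss to follow-up and "protocol violation by initiating pregnancy, dose taper, incarceration, or receipt of cancer or palliative care".
- The Table 3 footnote defines censoring class C2 to include "deviation from the trial exclusion criteria such as initiation of pregnancy, incarceration, dose taper, cancer or palliative care, leaving out of BC". The Table 3 row for deviation from inclusion/exclusion criteria shows C2 in the per-protocol column of all three outcomes, all-cause mortality included.

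The initiator analysis has no such stop: "For initiator analysis, follow-up ends at the earliest of outcome, death, loss to follow-up, 24 months after time zero, or December 31, 2022". Table 1 (Causal contrasts) gives an initiator analysis to sub-populations (i) to (viii) only; (ix) and (x) have the per-protocol analysis alone.

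Table 5 lists a per-protocol sensitivity analysis, "No episode discontinuation at receiving cancer or palliative care". It names no outcome, and its rationale concerns people who discontinue treatment, not deaths.

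On the rank of mortality, Key measures says "Time to OAT discontinuation and all-cause mortality will be primary outcomes of interest for the initiator analysis". The Abstract calls it primary without that limit. Table 1 instead lists discontinuation "along with the time to all-cause mortality and overdose-related acute care visit as the secondary outcomes".

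**The concern.** Palliative care is closely tied to approaching death. Someone who dies after a palliative care record enters the per-protocol mortality analysis as censored alive. The C2 weights replace that person with others who had the same Table 4 covariates a week earlier and no such record. Those stand-ins do not carry the risk that the record signals. Because the event itself ends follow-up, nobody is observed alive and uncensored after it, so there is no one to weight up.

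At stake is what the result means. Initiator and per-protocol mortality would share a name while counting different deaths, and a comparison of the two would mix the effect of adherence with the effect of this rule. For (ix) and (x), no other main analysis shows the omitted deaths.

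**Working it through.** The plan states no death rate, event rate or sample size on this point, so there is no figure to reproduce. The check compares the rules and then illustrates the size under assumed rates.

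**Rules side by side**

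| Event after time zero | Initiator, mortality | Per-protocol, mortality |
|---|---|---|
| Cancer or palliative care | follow-up continues | censored, C2 |
| Death after that event | counted | not counted |

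**What the weights can use.** Covariates are lagged one week (Initiator analysis). Table 4 has no palliative care or new-cancer item. The nearest proxy is the weekly updated Charlson index from hospital records. It can correct for illness visible before the event, but not for excess risk that begins with it.

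**Illustration 1: absolute risk, with weights assumed perfect on measured frailty.** Weekly model over 104 weeks; every rate is an assumption.

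- 15% of people are frail.
- Weekly death hazard before the event is 0.0004 (not frail) or 0.001 (frail).
- The weekly hazards of the event and of death after it are in the table.

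The censored, weighted risk uses only the pre-event death hazards:

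0.85 × (1 − 0.9996^104) + 0.15 × (1 − 0.999^104) = 0.85 × 0.0408 + 0.15 × 0.0988 = 0.0495, or 5.0%.

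The true risk adds deaths after the event. In the middle case:

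0.85 × (0.0405 + 0.0071) + 0.15 × (0.0940 + 0.0664) = 0.0645, or 6.5%.

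| Case | Weekly event hazard (not frail / frail) | Weekly death hazard after event | True 24-month risk | Censored, ideal weights | Shortfall | Deaths after event |
|---|---|---|---|---|---|---|
| Low | 0.00005 / 0.0005 | 0.02 | 5.6% | 5.0% | 0.6 points | 12% |
| Middle | 0.0001 / 0.001 | 0.03 | 6.5% | 5.0% | 1.5 points | 25% |
| High | 0.0002 / 0.002 | 0.05 | 8.4% | 5.0% | 3.4 points | 43% |

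As a control, if the event does not change the death hazard (0.0007 per week throughout), the true and censored risks agree at 7.0%. If one arm has twice the event incidence of the other (middle case against doubled event hazards), the true risk difference is 7.9% − 6.5% = 1.4 points and the censored one is 0.0.

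**Illustration 2: contrast between two arms.** Let o be the yearly rate of overdose-type death. Let i_low (85% of people) and i_high (15%) be the yearly rates of illness death, and k the share of illness deaths preceded by a record and so lost. The short lead time is ignored. Then

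risk = 1 − [0.85 × exp(−2(o + i_low(1 − k))) + 0.15 × exp(−2(o + i_high(1 − k)))],

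and the hazard ratio (HR) is approximated by the ratio of log survival.

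- Illness deaths differ (o = 2%, i_low = 0.3%, i_high = 4% versus 6%). At k = 0 the risks are 5.5% and 6.0%, a risk difference of 0.52 points and an HR of 1.10. At k = 0.3, 0.6 and 0.8 the risk difference is 0.38, 0.22 and 0.11 points and the HR is 1.08, 1.05 and 1.03.
- Only overdose-type deaths differ (o = 1.5% versus 2%, i_low = 0.3%, i_high = 4% in both arms). The risk difference stays at about 0.95 points. The HR moves from 0.82 to 0.81, 0.79 and 0.77.

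The rule therefore shrinks the contrast in one setting and moves the HR further from 1 in the other.

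**The case against.** Four points on the other side have weight.

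- **A reader might infer that deaths are deleted from a primary outcome.** The document does not support that in general. Key measures attaches the primary label to the initiator analysis, which counts these deaths for (i) to (viii), and Table 1 calls mortality secondary. The loss is confined to the per-protocol estimates.
- **A reader might infer that the emulation departs from its own target trial.** It does not. The target-trial column of Table 1 itself censors at the violations in Table 3, and the emulation column says the same. The fault is that this quantity carries the name all-cause mortality.
- **Measured history helps.** Charlson index, opioid dispensing outside OAT and psychiatric or sedative dispensing can absorb part of the dependence. This stands; the excess risk that starts with the event remains.
- **The analysis without this rule is already planned.** It is, but as a sensitivity analysis with no outcome named. For (ix) and (x) the main result would still be the censored one.

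There is also an arguable reason for the rule. The Introduction notes that SROM was first developed for pain, so dispensing after a cancer or palliative record may not represent OAT. That may justify stopping follow-up for discontinuation. It does not make a later death any less a death from any cause.

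**Conclusion.** The concern holds for per-protocol mortality. As planned, the analysis estimates mortality in the absence of cancer or palliative care. This rests on one assumption from outside the document: that such care, palliative care above all, raises the risk of death beyond what prior-week covariates show. Given that, absolute risks are too low for all-cause mortality. The 0.6 to 3.4 point shortfall illustrates assumed rates and is not an estimate for this cohort.

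A reader might go further and infer a bias for or against SROM. The document does not support that: it gives no event rates by arm, and the two settings in the second illustration move the contrast differently. The weight is moderate for (i) to (viii), where the initiator analysis keeps these deaths, and greater for (ix) and (x), where no other main analysis does.

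**What to change.** 1. For all-cause mortality, remove receipt of cancer or palliative care from the censoring events in Study follow-up, Per-protocol analysis and the C2 definition of Table 3. Make the Table 5 version the main per-protocol mortality analysis and keep the present rule as the sensitivity analysis.
2. Leave every other censoring rule in place, including the day-30 rule for clones in (ix) and (x). Switching off dose and switch censoring after the event would be wrong: a clone in the switch-to-SROM arm who never switched would stay past day 30, and a later death would count in that arm.
3. Amend the target-trial follow-up in Table 1 to match.
4. If the present rule stays as the main one, label the estimand as mortality without cancer or palliative care wherever it is reported.
5. Reconcile the Abstract and Key measures with Table 1 on whether mortality is primary.

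The cost is wording in three sections and two tables. The uncensored analysis is already planned, so little programming is added. Study status and timeline says that no analyses have been run, so the change can still be prespecified. The downside is small: some person-time after the diagnosis may not reflect usual OAT prescribing. The change concerns only what the analysis counts.

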### Covariate selection

We propose to include all selected confounders identified in a recent methadone versus buprenorphine/naloxone study,[61] which applied a modified disjunctive cause criterion[62] to the augmented list of covariates from systematic reviews.[63,64] These covariates include socio-demographic factors, measures of disease severity and comorbidity, and OAT-related factors. Additionally, COVID-19-related covariates will be included to control potential selection bias introduced by pandemic-related service disruptions and differential treatment accessibility (see Table 4 for the list of covariates).

All time-varying covariates will be updated weekly. These covariates will be used to estimate the inverse probability of treatment as well as censoring weights to adjust for measured confounding and informative censoring respectively.

